## Abstract

**Background:**

Femorotibial knee osteoarthritis is associated with muscle weakness in the lower limbs, particularly in the quadriceps, which results in disease progression. The interest of having muscular strengthening as part of the therapeutic arsenal for the medical treatment of knee osteoarthritis is now well established.

The functional disability induced by knee osteoarthritis manifests itself principally when walking, notably downhill, during which the muscles are called upon to contract eccentrically.

We can therefore think that eccentric muscular strengthening could bring a functional benefit that is superior to concentric muscular strengthening.

**Methods/Design:**

This is a prospective, randomized, bicenter, parallel-group, international study. Eighty patients aged from 40 to 75 years old, suffering from medical-stage knee osteoarthritis, will undertake 6 weeks of isokinetic muscular strengthening. Randomization determines the mode of muscular strengthening: either exclusively eccentric or exclusively concentric.

The principal objective is to demonstrate the superiority of the improvement in the quadriceps isokinetic torque after isokinetic muscular strengthening by the eccentric mode compared to the concentric mode.

The following parameters are also evaluated: the variations in the level of pain, the parameters of walking (maximum speed over 10 and 200 meters, analysis on a computerized Gaitrite™ treadmill), static equilibrium (on a FUSYO™ force platform), and the functional status of the patient using the Western Ontario and MacMaster Universities osteoarthritis index (WOMAC) questionnaire after the strengthening period and at 6 months.

**Discussion:**

A better knowledge of the most effective mode of muscular strengthening is needed to optimize the functional benefits to the patients. In case of superiority in terms of efficacy of the eccentric mode, the latter could be given priority in the rehabilitation treatment of knee osteoarthritis patients.

**Trial registration:**

Clinical trials.gov number: NCT01586130.

## Background

By 2020, the increase in life expectancy and the aging of the population should bring arthritis to fourth place in the causes of disability in developed countries [1].

The knee is one of the most frequent arthrosic locations. In 2002, it represented 1.7% of the health insurance expenses in France [2]. Its therapeutic care relies on the association of pharmacological and nonpharmacological treatments [3].

Patients suffering from knee osteoarthritis present a muscular weakness in the legs, particularly the quadriceps [4-6]. The extent of quadricep muscle deficiency is linked to the level of gonalgia and functional disability [7]. It has been proven that physical activity and muscular strengthening improves these two factors. On the other hand, we do not know which mode of muscular strengthening is the most efficient. The current recommendations suggest an adapted and personalized rehabilitation program concerning the type of exercises, the intensity, and the frequency [8]. Several studies have shown the interest of isokinetic dynamometers as rehabilitation tools in muscular strengthening and have found an equivalent or superior efficacy of this rehabilitation mode compared to the isometric or isotonic physical exercises more commonly used in current practice [9,10]. The isokinetic exercises also present an advantage in terms of cardiac tolerance, which is interesting for aged, potentially vascular, arthrosic patients. Indeed, it leads to a smaller increase in heart rate and blood pressure than isometric exercises [11].

The eccentric contraction of the quadriceps muscles seems to play a fundamental role in walking and other activities of everyday life, allowing control of the bending of the knee (cushioning) and an active joint stability [12]. The protocols for isokinetic muscular strengthening, in combined concentric-eccentric mode, have shown better results than the concentric mode alone in terms of functional improvement in knee osteoarthritis [13].

To our knowledge no published study has compared isolated eccentric strengthening to concentric strengthening alone in knee osteoarthritis (OA) whereas the superiority of eccentric strengthening in terms of increase in strength has been demonstrated elsewhere for other pathologies [14]. Thus, rehabilitation care currently practiced could be optimized by preferentially using this muscular strengthening contraction mode.

## Methods/Design

### Study participants

Patients will be recruited during consultations in Physical and Rehabilitation Medicine (PRM) and in Rheumatology in the hospital or in private practice. Patients’ rehabilitation histories and osteoarthritis therapies will be collected to fully appreciate possible cofounding biases. The selection criteria for patients for the ISOGO study are shown in Table 1.

**Table 1 T1:** Inclusion and exclusion criteria of ISOGO study

**Inclusion criteria**	Aged between 40 and 75 years old
	Knee osteoarthritis according to the criteria of the American College of Rheumatology
	Unilateral medial femorotibial knee osteoarthritis
	No corticosteroid or hyaluronic acid infiltration within the 2 months before inclusion
**Exclusion criteria**	Knee arthroplasty
	Radiological end-stage knee osteoarthritis: stage 4 of Kellgren and Lawrence classification
	Associated symptomatic femoropatellar osteoarthritis
	Language or mental issues preventing the understanding of the protocol
	Pregnancy

Patient eligibility will be defined as symptomatic knee OA in the medial compartment, fulfilling the American College of Rheumatology (ACR) clinical criteria for OA of the knee. Patients will be included at least 2 months after corticosteroid or hyaluronic acid injection.

Radiographs will be scored using the Kellgren Lawrence (KL) global classification, which assigns a number from 0 (normal) to 4 (severe) based on the presence of osteophytes, joint space narrowing, sclerosis and joint deformity. Patients with grade 4 KL radiological classification will be excluded from the study.

Authorization was obtained from the institute’s committee on human research (CPP Sud Est VI) in September 2011. Prior to enrollment in the study, all subjects will be asked to give their informed consent. Authorization from the AFFSAPS was obtained in September 2011. The study is registered with Clinical trials.gov under the number: NCT01586130.

### Study design

ISOGO is a prospective randomized double center clinical trial with blinded evaluation of the endpoints. The outline of the study is shown in Figure 1.

**Figure 1 F1:**
[figure not shown]
Study design: This flow-chart (to be read from left to right) displays the different phases of the protocol and explorations being conducted.

#### Randomization

Included patients will be randomly allocated to either arm (training group) in a 1:1 ratio. The randomization list will be generated by block randomization. Randomization will be performed automatically (using software) by an independent statistician once a patient will be considered eligible and informed consent will be obtained.

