#### Isokinetic training

All tests and training sessions will be completed on the HumacNorm Cybex 6000™ computer-controlled isokinetic dynamometer, which will be calibrated before every test.

Patients with medial femorotibial knee osteoarthritis will be recruited and randomized into two groups of 40:

1. Group A: (eccentric isokinetic training): 12 sessions of eccentric isokinetic extension-flexion repetitions of the affected knee.

2. Group B: (concentric isokinetic training): 12 sessions of concentric isokinetic knee extension-flexion repetitions of the affected knee.

Patients will have resistance training two times a week for 6 weeks (12 sessions) with a minimum of 1 day of rest between sessions in order to minimize the potential effect of delayed onset muscle soreness (DOMS).

Participants will begin each session with a 5-minute warm-up on a stationary cycle ergometer at low rate and low load. After warm-up, patients’ will complete extensor and flexor stretches under the supervision of the physiotherapist. The affected knee then will receive the rehabilitation treatment. The first session will consist of one set of five repetitions of reciprocal concentric or eccentric isokinetic knee extensions (according to randomization) and flexion with maximal effort. The number of sets of repetitions will progressively increased to achieve 12 sets of five repetitions on the last session.

To monitor progress and limit habituation to a specific contraction mode, the seventh session will be preceded by a repeat of the isokinetic testing evaluation completed at the baseline (testing on both the eccentric and concentric modes and on both knees).

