### Statistical considerations

#### Justification of the number of subjects to be included

The principal objective of this study lies in the assessment of the increase in the quadriceps isokinetic peak torque of the treated knee as measured using a Cybex Norm™ computerized dynamometer, with the concentric mode, at a speed of 60/second after treatment.

The estimation of sample size was determined on the basis of a greater improvement of muscular strength in the quadriceps of the treated knee (muscular strengthening in the medical treatment of the femorotibial knee osteoarthritis) in the eccentric group compared to the concentric group. From the work of Tüzun *et al.*[10] and Huang *et al*. [9], we learned about the increase in muscular strength of the quadriceps using isokinetic concentric training. The difference between the two groups was estimated at 15% (treated as quantitative) and the standard deviation was fixed at 20 (supposedly identical in the two groups). Also, for a type I error α and a statistical power fixed respectively at 5% (in a two-sided situation) and 90%, 40 patients per group need to be recruited. The rate of ‘lost to view’ for the measurement of the principal endpoint criterion at 6 weeks is considered negligible [10].

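### In a two-centre trial the principal comparison names no centre term; centre would enter only if it happened to look unbalanced, at a modest cost in precision

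*Protocol article*

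**What the plan says.** The Abstract (Methods/Design) states: "This is a prospective, randomized, bicenter, parallel-group, international study". The Study design section repeats the point: "ISOGO is a prospective randomized double center clinical trial with blinded evaluation of the endpoints".

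The Randomization section gives the ratio ("Included patients will be randomly allocated to either arm (training group) in a 1:1 ratio") and the method ("The randomization list will be generated by block randomization"). It adds that an independent statistician allocates by software after eligibility and consent. Block size and strata are not mentioned. The Isokinetic training section gives the arm sizes: patients are "recruited and randomized into two groups of 40".

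The Principal analysis section compares the six-week gain in concentric quadriceps torque at 60°/s by a Student test, or a Mann-Whitney test if the Student assumptions fail. It does so first without adjustment and then with adjustment for factors whose distribution turns out uneven between the arms. No covariate is named. The Secondary analysis section carries the same approach to the secondary endpoints.

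**The concern.** Centre is known before any patient is randomised, and in this trial it plausibly affects the outcome. Training is maximal-effort exercise delivered on site, and the endpoint is torque under verbal encouragement, so local staff can influence both. The analysis rule nevertheless treats centre like any unforeseen covariate and admits it only if imbalance is noticed.

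That rule works poorly in either case:

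- **If the list is stratified by centre**, the arms are balanced on centre by construction. The rule would then never select centre, although the analysis should reflect the stratification.
- **If the list is not stratified**, blocks balance the arms overall but not within a centre. A centre difference in torque gain can then fall unevenly on the arms by chance. Whether it is corrected depends on a judgement made after seeing the data.

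In both cases, variation between centres stays in the error term of the unadjusted test.

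**Working it through.** **Inputs from the protocol article.** Difference 15, SD 20, two-sided alpha 5%, power 90%, 40 per arm, negligible loss at 6 weeks (Justification of the number of subjects to be included).

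**Inputs assumed, because the article gives none.** Centre shares (equal unless stated), block sizes of 4 or 8, and a difference D between centres in mean gain of 0, 5 or 10 points. The planned SD of 20 is taken as the SD within a centre.

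**1. The plan's own figure.** n = 2(1.960 + 1.282)² × 20² / 15² = 2 × 10.51 × 400 / 225 = 37.4, so 38 per arm. The exact t calculation gives 38.35, so 39. The stated 40 is reproduced within rounding. Power of the t test at 40 per arm is 0.912.

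**2. Chance imbalance under one unstratified list.** With 80 patients, 40 eccentric and 40 in each centre, the number of eccentric patients in a centre is approximately hypergeometric.

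- Variance = 40 × ½ × ½ × (80 − 40)/79 = 5.06, so SD = 2.25.
- The 95% range is 16 to 24.
- P(24/16 or worse) = 0.117.

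A simulation with blocks of 4 or 8, and 50%, 70% or 80% of patients in the larger centre, gives the following for the gap between arms in centre share:

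- 10 percentage points or more in about 40–51% of trials;
- 20 points or more in about 4–12%;
- a 95th percentile of 15 to 20 points.

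Block size hardly matters.

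**3. Effect on the contrast.** Shift = (gap in centre share) × D. For a 24/16 split the gap is 24/40 − 16/40 = 0.20.

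- D = 10: 0.20 × 10 = 2 points of the planned 15.
- D = 5: 0.20 × 5 = 1 point.

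**4. Effect on power, equal centres.** Without the centre term and without stratification, the total SD is √(20² + D²/4). For D = 10 this is √425 = 20.62, the standardised difference is 15/20.62 = 0.728, and power is 0.895. With the centre term, the SD stays at 20. The variance of the contrast is then multiplied by 1/(1 − g²), where g is the gap in centre share. Averaged over the distribution in step 2, with 77 degrees of freedom, power is 0.908.

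Formula and simulation together give:

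| D | Unstratified: no term | Unstratified: with term | Stratified: no term | Stratified: with term |
|---|---|---|---|---|
| 0 | 0.912 | 0.908 | 0.912 | 0.912 |
| 5 | 0.908 | 0.908 | 0.910 | 0.912 |
| 10 | 0.895 | 0.908 | 0.901 | 0.912 |

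Separate simulation runs for the unstratified D = 10 case gave 0.893–0.897 without the term and 0.904–0.910 with it.

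**5. Type I error of the unadjusted test.**

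- Unstratified: about 0.050 at D = 10 with equal centres; 0.047–0.048 in smaller runs with a 70/30 split.
- Stratified, D = 10, equal centres: about 0.044, which is conservative. With the centre term it returns to about 0.050.

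There is no inflation in either case.

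**The case against.** The strongest objection is that this is a condensed article. Stratification factors are often left to the full protocol or analysis plan, and the Randomization section neither states nor excludes them. That stands. A reader might infer that allocation ignores centre, but the text does not support this, since a stratified list is also a list generated in blocks. What remains is the analysis rule, which the article does state.

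Second, the planned adjusted comparison could pick up a poor split such as 24/16. That is partly right, but it works only when imbalance is seen. It cannot recover precision when centre is balanced but still predicts the outcome.

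Third, the effect is small. That is also right: if centres differ by 5 points, the term gains almost nothing, and if they do not differ, it costs a little.

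Three further readings are tempting but unsupported:

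- **Different machines at the two sites.** The Isokinetic training section says "All tests and training sessions will be completed on the HumacNorm Cybex 6000™ computer-controlled isokinetic dynamometer, which will be calibrated before every test", while the sample-size section has the endpoint "as measured using a Cybex Norm™ computerized dynamometer". This is an inconsistency in naming. No section assigns a model to a centre, and a constant device offset cancels in an absolute within-patient change. It is not evidence of site differences.
- **Bias in favour of one arm.** Chance imbalance has no preferred direction, the standard error already allows for it, and the isokinetic evaluator is to be blinded.
- **Two countries with different practice.** No country is named. International status combined with two centres only suggests it.

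**Conclusion.** The point holds as a recommendation on the analysis. In a two-centre trial the stated rule leaves centre out of the principal comparison unless it looks unbalanced, and a centre term fixed in advance is better under either form of allocation. The consequence is modest: about one percentage point of power at an assumed 10-point centre difference with equal centres, almost none at 5 points, and a loss of at most about 0.005 if centres do not differ. An unstratified list would bring a 24/16 split or worse in about 12% of trials, and at exactly 24/16 the contrast moves by 2 points of 15. The sample size is unaffected. Centre shares, block size and the centre difference are all assumptions. The documents do not show that the list is unstratified, that the result is biased, or that type I error is inflated.

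**What to change.** Prespecify centre as a fixed effect in the primary and secondary comparisons, whatever the observed balance and whether or not the list is stratified. For the primary endpoint this can be a linear model of torque gain on arm and centre. If a rank test is kept as the fallback, use its centre-stratified form (van Elteren) in place of the plain Mann-Whitney test. The change costs one degree of freedom and no patients, and it can be made at any time before unblinded data are reviewed.

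State in the protocol whether the block list is stratified by centre. If it is not, move to separate block lists by centre for patients still to be randomised, but only if this can be done without disrupting allocation. The Trial status section reports active recruitment since April 2012, so changing the list is a change to a running procedure and not free. The centre term is worth having without it.

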#### Isokinetic training

All tests and training sessions will be completed on the HumacNorm Cybex 6000™ computer-controlled isokinetic dynamometer, which will be calibrated before every test.

Patients with medial femorotibial knee osteoarthritis will be recruited and randomized into two groups of 40:

1. Group A: (eccentric isokinetic training): 12 sessions of eccentric isokinetic extension-flexion repetitions of the affected knee.

2. Group B: (concentric isokinetic training): 12 sessions of concentric isokinetic knee extension-flexion repetitions of the affected knee.

Patients will have resistance training two times a week for 6 weeks (12 sessions) with a minimum of 1 day of rest between sessions in order to minimize the potential effect of delayed onset muscle soreness (DOMS).

Participants will begin each session with a 5-minute warm-up on a stationary cycle ergometer at low rate and low load. After warm-up, patients’ will complete extensor and flexor stretches under the supervision of the physiotherapist. The affected knee then will receive the rehabilitation treatment. The first session will consist of one set of five repetitions of reciprocal concentric or eccentric isokinetic knee extensions (according to randomization) and flexion with maximal effort. The number of sets of repetitions will progressively increased to achieve 12 sets of five repetitions on the last session.

To monitor progress and limit habituation to a specific contraction mode, the seventh session will be preceded by a repeat of the isokinetic testing evaluation completed at the baseline (testing on both the eccentric and concentric modes and on both knees).

### Objectives and endpoints

The primary objective of this study will be to assess whether eccentric isokinetic strengthening improves the isokinetic strength of the quadriceps more than concentric isokinetic strengthening in patients with medial femorotibial knee osteoarthritis. The concentric isokinetic torque of the quadriceps will be used as primary outcome measure because of its better reliability and reproducibility compared to an eccentric isokinetic torque [15].

The secondary objectives will be to compare the effects of concentric and eccentric isokinetic training on:

1. Static postural balance on a Fusyo™ force platform

2. Temporospatial gait parameters assessed by Gaitrite™

3. Maximal 10 meters and 200 meters at walking speed

4. Range of knee motion

5. Pain, stiffness and function assessed by the Western Ontario and MacMaster Universities osteoarthritis index (WOMAC) questionnaire.

These access joint mobility but also physical function in daily living activities, which influence improved feeling for the most patients. The effects of 6 weeks of training on these parameters will be evaluated after the 12 strengthening sessions and at 6 months. The possible adverse effects of the different strengthening modes will also be analyzed (muscular and articular pain evaluation before and after each session, maximal cardiac frequency during sessions, and muscular lesions).

### Assessments

#### Isokinetic tests

Subjects will seat with the backrest at a 90° angle and instructed to grip the sides of the seat during the test. The thigh, pelvis, and trunk will be stabilized with straps. An adjustable lever arm will be attached to the subject’s leg by a padded cuff just proximal to the lateral malleolus. The axis of rotation of the dynamometer arm will be positioned just lateral to the lateral femoral epicondyle.

Conventional concentric and eccentric continuous isokinetic tests will be used. During concentric and eccentric tests, the subjects will continuously push the lever arm of the isokinetic device up and down through the whole range of motion between 10° and 90° (0°: straight leg) to measure quadriceps and hamstring strength. Subjects will not systematically have prior experience with the isokinetic dynamometer and will familiarize themselves with testing procedures by performing three consecutive warm-up trials for each muscle group and speed.

During tests the subjects will perform five maximal continuous flexion-extension repetitions of both legs at each angular velocity: 60°/s and then 180°/s in concentric mode and 30°/s in eccentric mode (according to the randomization). During the concentric tests the speed order will be from slower to faster, as suggested by Wilhite *et al*. [16]. A 1-minute rest will be allowed between each contraction speed. Eccentric tests will be performed after the concentric tests. A 5-minute rest will be allowed between legs. The researcher conducting the isokinetic evaluation will be blinded to the strengthening mode received by the patient. The subjects will be verbally encouraged to exert maximal effort.

#### Clinical examination at inclusion

The following data will be recorded:

1. Knee medical history;

2. Range of motion of the knee;

3. Thigh circumference at 5, 10 and 15 cm from the base of the patella;

4. Blood pressure,

5. Heart rate;

6. Anthropometric measurements (height, weight, body mass index); and

7. Electrocardiogram.

#### Western Ontario and MacMaster Universities osteoarthritis index self-questionnaire

Patients’ pain, stiffness and physical function will be assessed using the administered WOMAC questionnaire. This activity-based questionnaire includes 24 questions (five on pain, two on stiffness and 17 on physical function disability) and has been shown to be a reliable and valid multidimensional health status instrument in knee and hip OA.

